### Statistical analyses

Univariate descriptive statistics (means and standard deviations or medians and interquartile ranges, numbers, and percentages) will be used to summarise participant characteristics at baseline overall and by randomised group and check for skewed distributions. All trial analyses will be performed including participants in the groups to which they were randomised (based on the intention-to-treat principle), but excluding individuals with missing outcome data.

For the primary outcome, intervention effects will be estimated using a linear regression model of change in risk relative to an individual with a recommended lifestyle (risk at three months follow-up minus risk at baseline), with the baseline value included as a covariate in the model (i.e. analysis of covariance, ANCOVA). The missing indicator method [54] will be used to enable individuals with missing values of the outcome at baseline to be included. An F-test will be performed of the null hypothesis that there is no difference between the four randomised groups. The model will also be used to derive estimates and confidence intervals from four pairwise comparisons: 1) Control group vs the three risk groups combined; 2) bar chart risk presentation vs pictographs; 3) bar chart risk presentation vs qualitative scale; and 4) pictographs vs qualitative scale. Multiplicative interactions between the interventions and each of the following variables will be tested using an F-test: age (≤ or > 40 years), sex, baseline risk relative to an individual with a recommended lifestyle (≤ or > 1.5), self-perceived risk at baseline below or above estimated risk or numeracy (< or ≥ two correct answers). If the *p*-value for interaction with one of the above variables is < 0.05, then estimates and confidence intervals for each of the pairwise comparisons will be derived within each subgroup defined by that variable.

Similar analyses will be used to estimate intervention effects on continuous secondary outcome variables. Smoking status (current vs ex-smoker and non-smoker) and accuracy (correct/incorrect) at three months follow-up will be analysed using binary logistic regression models, with adjustment for their respective values at baseline; randomised groups will be compared using a likelihood ratio test, and the four pairwise differences (risk ratios) and confidence intervals will be estimated. Intention to change behaviour, self-efficacy and response efficacy are only measured immediately after the intervention so linear regression will be used.

For all outcomes, 98.75% confidence intervals will be presented (based on a Bonferroni corrected significance threshold of 1.25%) to acknowledge the fact that four pairwise comparisons are presented. For any particular outcome, this is a conservative approach since the comparisons are not all independent of each other.

Acceptability, usefulness of the risk and/or lifestyle information, and process measures relating to use of the intervention will be summarised across the four groups using descriptive statistics (means, standard deviations, numbers, and percentages).

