### Randomisation, allocation concealment and blinding

The baseline questionnaires and all study materials will be developed within the Gorilla.sc research platform (www.gorilla.sc/about). Gorilla is a bespoke software program that allows researchers to develop online questionnaires and interactive tasks. Participants will be randomised 1:1:1:1 to the four groups at an individual level using a computer program built into the Gorilla research platform based on computer generated random numbers within block sizes of eight. Randomisation will be stratified by sex, risk relative to an individual with a recommended lifestyle (≤ or > 1.5) and age (≤ or > 40 years). Given the nature of the trial, it is not possible to blind participants to which intervention they receive. The researchers assessing the trial outcomes will remain blinded to the allocation of individuals until generation of the final dataset for analysis.

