### Sample size

The target sample size is 1000 participants (250 per group). In the EPIC-Norfolk cohort [54] the mean risk of developing one or more of the five chosen cancers relative to an individual with a recommended lifestyle is 1.77 (SD 0.97). It is likely that the baseline and follow-up values of the outcome will be correlated, but the size of this correlation is unknown. To detect a baseline-adjusted between-group difference of 0.3 with a significance level of 1.25%, assuming the SD is 0.97 and 10% loss to follow-up, the power will be 79, 80% or 83% if the correlation is assumed to be 0.1, 0.2 or 0.3.

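### The 1:3 control contrast and the format pairs come from one linear model with, by default, one residual variance; if the intervention changes the spread, their intervals err in opposite directions by an amount the protocol does not fix

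*Protocol article*

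**What the plan says.** In the protocol article, Statistical analyses, the primary analysis is an ANCOVA of change on baseline across all four arms: "intervention effects will be estimated using a linear regression model of change in risk relative to an individual with a recommended lifestyle". The global test comes from it: "An F-test will be performed of the null hypothesis that there is no difference between the four randomised groups". So do the contrasts: "The model will also be used to derive estimates and confidence intervals from four pairwise comparisons". The list begins "1) Control group vs the three risk groups combined; 2) bar chart risk presentation vs pictographs", and the other two are the remaining format pairs. Intervals are at 98.75%, a Bonferroni level for four comparisons, and similar analyses apply to continuous secondary outcomes.

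Randomisation, allocation concealment and blinding states: "Participants will be randomised 1:1:1:1 to the four groups at an individual level". The first contrast is therefore 1:3 and the others 1:1.

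Sample size gives a mean of 1.77 and a single SD of 0.97 for the outcome measure in a reference cohort, and plans "To detect a baseline-adjusted between-group difference of 0.3 with a significance level of 1.25" per cent, allowing 10% loss to follow-up. No arm-specific SD is given. The text does not say whether the effect is a constant shift or proportional, and it says that the baseline–follow-up correlation is unknown.

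**The concern.** An ordinary linear model estimates one residual variance from all arms. Here three of the four arms contributing to it are risk arms, while the variance of the first contrast depends mainly on the single control arm. If the risk arms have a smaller spread than control, the pooled value is too small for "Control group vs the three risk groups combined" and too large for the format pairs. If they have a larger spread, both errors reverse.

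A change of spread is plausible. The outcome is a ratio to a recommended lifestyle, so the mean excess over 1 is 1.77 − 1 = 0.77, and the planned difference of 0.3 is 0.3/0.77 = 39% of it. People with more excess risk have more to change, and the lifestyle advice is tailored to the behaviours relevant to each person. At stake is whether the 98.75% intervals have their stated coverage when the intervention does something.

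**Working it through.** **Inputs.** From the protocol: 1:1:1:1 allocation; 250 per arm less 10% = 225; mean 1.77; SD 0.97; difference 0.3; significance level 1.25% (two-sided critical value 2.498). Assumed, because the protocol does not give them: k, the ratio of residual SD in each risk arm to that in control; the shape of the effect; and the baseline–follow-up correlation r in the simulations.

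**Step 1: reproduce the stated power.** SE = 0.97 × √(1 − r²) × √(2/225); power = Φ(0.3/SE − 2.498).

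| r | SE | Power | Stated |
|---|---|---|---|
| 0.1 | 0.0910 | 78.8% | 79% |
| 0.2 | 0.0896 | 80.2% | 80% |
| 0.3 | 0.0872 | 82.7% | 83% |

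The figures reproduce as one arm against one arm with a common SD. The plan's own working assumption is thus k = 1.

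**Step 2: closed form.** In units of the control variance, with equal arm sizes:

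- pooled variance P = (1 + 3k²)/4
- control against three arms: model SE / true SE = √[P × (4/3) / (1 + k²/3)]
- format pair: model SE / true SE = √[P / k²]

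For k = 0.47/0.77 = 0.61: P = 0.529. The first ratio is √(0.529 × 1.333/1.124) = 0.79 and the second √(0.529/0.373) = 1.19.

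| Case | k | Contrast 1 ratio (coverage) | Format ratio (coverage) |
|---|---|---|---|
| Constant shift | 1.00 | 1.00 (98.75%) | 1.00 (98.75%) |
| Whole ratio scaled, 1.77 to 1.47 | 0.83 | 0.91 (97.7%) | 1.05 (99.2%) |
| Follow-up excess scaled, 0.77 to 0.47 | 0.61 | 0.79 (95.2%) | 1.19 (99.7%) |
| Risk arms more variable | 1.2 | 1.10 (99.4%) | 0.96 (98.4%) |

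Coverage is 2Φ(2.498 × ratio) − 1.

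**Step 3: simulation of effect shapes.** 225 per arm, skewed outcome, ANCOVA on change, mean effect 0.3 unless stated, r between 0.1 and 0.8. Entries are model SE / true SE.

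| Shape of effect | Contrast 1 | Format pairs |
|---|---|---|
| Constant shift | 0.98–1.02 | 1.00–1.01 |
| 39% of baseline excess removed | 0.90–0.98 | 1.00–1.03 |
| Whole ratio scaled | 0.89–0.93 | 1.04–1.06 |
| Follow-up excess cut by 39% in every risk arm | 0.76–0.81 | 1.17–1.23 |
| 39% of people move fully to the recommended level | 0.94 (r = 0.1–0.3), 1.06 (r = 0.8) | 1.03–1.04, then 0.99 |
| Partial responders | up to 1.20 | 0.94–0.98 |
| Individually varying shift (SD 0.6) | 1.09–1.20 | 0.92–0.97 |

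With no effect in any arm the variances are equal, and the simulated type I error of contrast 1 was 1.1–1.5% against 1.25%. HC3 standard errors stayed within about 5% of the true value in the simulated cases and matched the ordinary ones, to simulation error, under equal variances.

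**The case against.** The strongest reply is that the protocol never states a pooled variance. It names a linear regression, and HC3 is compatible with that text. The variance estimator is also something a protocol article commonly leaves to the analysis plan, which is not shown. This stands: it is why the point is an improvement and not an error.

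A reader might infer that the plan's own mean, SD and target difference imply a 20% distortion. They do not. The single SD of 0.97 implies none. The 20% needs the added assumption that the whole follow-up excess, including the part unrelated to baseline, shrinks by 39% in every risk arm. If people instead remove 39% of the excess they had at baseline, which is the risk they are shown, the ratio for contrast 1 is 0.90–0.98. Nor is 1 a strict floor: the reference lifestyle has a BMI of 25, five portions of fruit and vegetables and 150 minutes of activity, and people can do better than some of these.

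A reader might also infer a wrong conclusion on the main question, or lost power for formats. Neither is shown. In the 20% case contrast 1 was detected in 99.6–100% of trials with model standard errors and 98.7–99.9% with the true one. That case gives all three risk arms the same effect, so there is no format difference to detect.

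What survives is that direction and size are unknown in advance, which favours an estimator that does not need equal variances.

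**Conclusion.** The point holds in a limited, conditional form. Under the default reading, intervals for the 1:3 contrast and for the format pairs err in opposite directions whenever the intervention changes the residual spread.

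- No effect, or a constant shift: no distortion.
- Proportional effect averaging 0.3: contrast 1 about 2–20% too narrow and format pairs up to about 20% too wide. The upper end belongs only to a 39% cut in follow-up excess in every risk arm, where the nominal 98.75% interval for contrast 1 covers about 95%.
- Only some people respond, with strong baseline–follow-up correlation: contrast 1 up to about 20% too wide and format pairs about 2–6% too narrow (up to 8% in the varying-shift simulation).

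The effect shape, k and r are assumptions throughout. The stated power figures are correct. The type I error is unaffected when all four arms are equal, so the global F-test under its own null is not called into question. No distortion has been shown for the secondary outcomes.

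**What to change.** In Statistical analyses, keep the model and the ANCOVA point estimates, and add one sentence: tests and 98.75% confidence intervals for the primary outcome use a heteroscedasticity-consistent (HC3) covariance matrix, or arm-specific residual variances. The same option may be used for continuous secondary outcomes for consistency.

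If the separate analysis plan already says this, nothing more is needed. The cost is one sentence and one software option. No extra participants or data are required, and under equal variances the intervals are essentially unchanged at 225 per arm.

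### The main models leave out stratification factors (sex, age and, beyond the primary outcome, baseline relative risk), so linear-model standard errors will be too large if those factors are prognostic

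*Protocol article*

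**What the plan says.** All references are to the protocol article.

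- **Randomisation, allocation concealment and blinding:** "Participants will be randomised 1:1:1:1 to the four groups at an individual level", using "computer generated random numbers within block sizes of eight". "Randomisation will be stratified by sex, risk relative to an individual with a recommended lifestyle" (cut at 1.5) and age (cut at 40 years). That makes eight strata.
- **Statistical analyses, primary outcome:** change in relative risk is regressed on randomised group "with the baseline value included as a covariate in the model (i.e. analysis of covariance, ANCOVA"). No other covariate is named.
- **Statistical analyses, continuous secondary outcomes:** "Similar analyses will be used to estimate intervention effects on continuous secondary outcome variables".
- **Statistical analyses, binary outcomes (smoking status, accuracy):** logistic models "with adjustment for their respective values at baseline".
- **Statistical analyses, outcomes without a baseline:** "Intention to change behaviour, self-efficacy and response efficacy are only measured immediately after the intervention so linear regression will be used".

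Sex, age group and baseline risk group do appear in Statistical analyses, but only as variables to be tested for interaction with the intervention. Nothing in the article puts the stratification factors into the main between-group models.

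**The concern.** Stratified blocking keeps the arms nearly balanced on sex, age group and risk group. The part of the outcome that these factors predict therefore contributes little to the true sampling variation of a between-arm difference. A linear model without the factors still counts that part as residual variance. If the factors predict the outcome, the model reports a larger standard error than the estimator really has. The 98.75% intervals then cover more often than they claim, tests run below 1.25%, and power is lower than the same data could give.

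Planned power is 79% to 83%, and the article already calls its Bonferroni threshold conservative, so there is little reason to add further conservatism. The outcomes most exposed are intention, self-efficacy and response efficacy. They have no baseline value to absorb any of this variation, and intention is among the secondary outcomes named in the objectives.

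**Working it through.** **1. The plan's own power.** Inputs from Sample size: 250 per group with 10% loss, so 225 analysed; difference 0.3; SD 0.97; level 1.25%. Sidedness is not stated; two-sided is assumed, in line with the 98.75% intervals, giving z = 2.4977.

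SE = 0.97 × √(1 − r²) × √(2/225); power = Φ(0.3/SE − 2.4977).

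| r | SE | 0.3/SE | Power | Stated |
|---|---|---|---|---|
| 0.1 | 0.0910 | 3.297 | 78.8% | 79% |
| 0.2 | 0.0896 | 3.348 | 80.2% | 80% |
| 0.3 | 0.0872 | 3.439 | 82.7% | 83% |

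The stated power reproduces. It assumes adjustment for the baseline value only, which is the planned primary model.

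**2. What each main model omits.**

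| Outcome | Named covariate | Stratification factors left out |
|---|---|---|
| Primary | Baseline relative risk, continuous | Sex, age |
| Continuous secondary with a baseline | Own baseline value | Sex, age, baseline relative risk |
| Intention, self-efficacy, response efficacy | None named | Sex, age, baseline relative risk |
| Smoking status, accuracy (logistic) | Own baseline value | Sex, age, baseline relative risk |

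**3. Size in a linear model.** Let R² be the share of the planned model's residual variance that the omitted factors explain. The article gives no value, so R² is an assumption shown as a range. With allocation balanced on the factors, the true SE is √(1 − R²) times the reported SE.

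- Reported SE relative to true SE: 1/√(1 − R²)
- True level: 2 × [1 − Φ(2.4977/√(1 − R²))]
- Power unadjusted: Φ((3.348 − 2.4977)/√(1 − R²))
- Power adjusted: Φ(3.348/√(1 − R²) − 2.4977)

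For 225 versus 225 at r = 0.2:

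| R² | SE too large by | True level | Power unadjusted | Power adjusted | Gap (points) |
|---|---|---|---|---|---|
| 0 | 0 | 1.25% | 80.2% | 80.2% | 0 |
| 2% | 1.0% | 1.16% | 80.5% | 81.2% | 0.7 |
| 5% | 2.6% | 1.04% | 80.9% | 82.6% | 1.7 |
| 10% | 5.4% | 0.85% | 81.5% | 84.9% | 3.4 |

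True coverage is 100% minus the true level: 98.75%, 98.84%, 98.96% and 99.15%.

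**4. Control versus the three risk groups combined.** With 225 versus 675 and the same inputs, SE = 0.97 × √0.96 × √(1/225 + 1/675) = 0.0732. Then 0.3/SE = 4.100 and power is 94.6%. Omission costs 0.3, 0.6 and 1.2 points at R² of 2%, 5% and 10%.

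**5. Simulation.** Each scenario used 3000 trials with stratified blocks of eight, 10% loss, r = 0.2 and a difference of 0.3. Here the fully adjusted residual SD is held fixed, so stronger factors lower the unadjusted power; in step 3 the planned model's residual SD is held fixed. Effects are in the units of the outcome and are assumptions.

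| Model as planned | Assumed effects | Mean SE, planned vs adjusted | Power, planned vs adjusted |
|---|---|---|---|
| Baseline only | None | 0.0896 vs 0.0897 | 79.8% vs 79.9% |
| Baseline only | Sex 0.2, age 0.2 | 0.0906 vs 0.0897 | 79.0% vs 79.8% |
| Baseline only | Sex 0.4, age 0.4, risk group 0.2 | 0.0937 vs 0.0897 | 76.0% vs 79.6% |
| No covariate | 0.2 each | 0.0942 vs 0.0897 | 75.3% vs 79.5% |
| No covariate | Sex 0.4, age 0.4, risk group 0.2 | 0.0969 vs 0.0897 | 73.7% vs 79.8% |

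In the last two rows the adjusted model also holds continuous baseline relative risk, so part of the gap comes from that term. With no true difference, the last row's planned model rejected in about 0.7% of trials against a nominal 1.25%. The Monte Carlo standard error at 1.25% is √(0.0125 × 0.9875/3000) = 0.2 points.

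**The case against.** The strongest reply is that the loss is conditional, and probably small where it matters most. The primary model already contains one stratification factor in continuous form. Moreover, under Risk estimates the reference risk for a recommended lifestyle is calculated by sex and ten-year age group, so much of the age and sex difference in absolute risk is divided out of the outcome by construction. What remains is whether sex and age predict three-month change given baseline. That stands, and it places the primary outcome at the low end of the range.

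The article could also leave a full covariate list to an unseen analysis plan, and plain linear regression does not literally mean unadjusted. This carries some weight for the three post-only outcomes. It carries less overall, because the article does name the adjustment for the other model classes, and the named set does not match the randomisation.

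Several stronger readings are tempting but not supported:

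- *The trial is underpowered or its power is misstated.* The stated 79/80/83% reproduces for the model as planned. The loss is relative to a better model.
- *The results would be biased or falsely positive.* The linear estimates are not biased, and any error in level is conservative.
- *The benefit of stratifying is thrown away.* The estimator keeps it; only the reported standard error fails to show it. Unadjusted power in step 3 rises with R² for that reason.
- *Risk perception, worry and anxiety suffer as much as intention.* They have their own baseline values, which should absorb much of any stable sex or age difference.
- *The same inflation applies to the logistic models.* It does not. Adding covariates there changes the conditional odds ratio and generally enlarges its standard error.
- *The power figures describe secondary outcomes.* They belong to the primary design point; no power is planned for the others.

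**Conclusion.** The mismatch between the stratified randomisation and the stated covariates is certain; its cost is not. It rests on an R² that the article does not give. At R² of 0 nothing is lost. Over 2% to 10%, a 225 versus 225 linear contrast at the primary design point has standard errors 1.0% to 5.4% too large and forgoes 0.7 to 3.4 points of power. The pooled comparison with control forgoes 0.3 to 1.2 points.

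For the primary outcome the low end is the more likely. For intention, self-efficacy and response efficacy the loss could be larger: about 4 to 6 points in the two simulated scenarios (79.5 − 75.3 = 4.2; 79.8 − 73.7 = 6.1), which borrow the primary outcome's difference and SD purely as an illustration. This is a worthwhile efficiency correction and does not threaten the trial's validity.

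**What to change.** Add a sentence to Statistical analyses stating that the linear between-group models include sex, age and baseline relative risk, either as continuous variables (age and risk) or as the strata used, alongside the outcome's own baseline value where one exists. For the primary outcome this means adding sex and age to the existing ANCOVA. Priority goes to intention, self-efficacy and response efficacy, where plain linear regression should be replaced by this adjusted model.

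For smoking status and accuracy, include the same factors for consistency with the design, and derive the planned risk ratios by standardising over the covariates. The SE figures above are no argument for that part.

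The cost is a sentence or two. Under Baseline assessment, the questions needed for the risk calculation, which include age and sex, are compulsory and are answered before randomisation. No new data are needed, and no participant is lost through missing covariates.

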#### Secondary objectives

The secondary objectives are to evaluate the effect of providing different formats of personalised cancer risk information alongside lifestyle information on: perceived risk of cancer; anxiety; cancer-related worry; intention to change behaviour; and awareness of cancer risk factors.

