Red meat consumption (portions per week)	✓	–	✓
Processed meat consumption (portions per week)	✓	–	✓
Secondary outcome measures			
Awareness of cancer risk factors	✓	✓	✓
Risk perception	✓	✓	✓
Risk conviction	✓	✓	✓
Self-efficacy	–	✓	–
Response-efficacy	–	✓	–
Maladaptive coping	✓	✓	✓
Intention to change behaviour	–	✓	–
Worry (Lerman cancer worry scale)	✓	–	✓
Anxiety (short-item SSAI)	✓	✓	✓
Potential mediators and moderators			
Numeracy	✓	–	–
Time orientation	✓	–	–
Self-rated general health	✓	–	–
Previous information on risk of developing cancer	✓	–	–
Cognitive evaluation of provision of cancer risk scores:			
Acceptability/usefulness etc. of information	–	✓	–

All secondary outcomes and potential moderators and mediators are also measured via self-report. Perceived risk is measured using the tripartite risk perception (TRIRISK) model [15] which includes deliberative, affective and experiential components of perceived risk. After questions about both absolute and comparative risk, we will also collect data on risk conviction using two questions (‘How certain are you about your answer to the above question / How confident are you that the estimate you gave in response to [the question above] is accurate, that is, that it reflects your actual risk?’) on 7-point Likert response scales from 1 (*Not at all certain / Not at all confident) to 7 (Extremely certain / Extremely confident*). These questions are included to allow assessment of whether risk conviction improves how well the construct of perceived risk predicts behaviour. They are adapted from suggestions in the literature [16] and are currently also being tested in a study in the US (personal report).

We will also collect data on cancer-related worry and anxiety using the Lerman cancer worry scale [42, 43] and the short-form of the state scale of the Spielberger State Trait Anxiety Inventory (STAI) [44] respectively. The Lerman cancer worry scale has been widely used in the literature [45, 46] and the short-form STAI consists of 6 items that comprise the most highly correlated state anxiety-present and state anxiety-absent items from the full-form of the STAI. Scores obtained using this short-form have been shown to be highly correlated with scores obtained using the full-form of the STAI [44]. Maladapative behaviours will be assessed using three statements adapted from Rippetoe and Rogers [47] and awareness of cancer risk factors using question six from the Cancer Awareness Measure [48].

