Overall intention to change behaviour will be measured immediately post intervention using four questions on 7-point Likert response scales from 1 (*Strongly disagree*) to 7 (*Strongly agree*) as in Ferrer et al.*,* [15] (‘I am determined to do everything I can to avoid getting cancer in the future.’/ ‘I am committed to engaging in behaviours that protect me against getting cancer in the future.’ / ‘I fully intend to have a lifestyle that will prevent me from getting cancer in the future.’ / ‘I will try to do all I can to avoid getting cancer in the future.’). Intention to change for each of the seven key lifestyle behaviours will also be asked separately using one item for each (e.g. ‘I intend to be more physically active in the next three months’) on a 5-point Likert response scale from 1 (*Strongly disagree*) to 5 (*Strongly agree*) with a sixth option ‘*Not applicable*’. Response efficacy and self-efficacy will both be measured using three items for physical activity and three items for diet as used in previous research [49, 50].

Self-rated health, family history of cancer, numeracy and time orientation will also be measured at baseline. Numeracy will be assessed using the 3-item Schwartz scale [51] adapted for the UK. Time orientation, the extent to which individuals tend to be motivated more by future or present goals when making decisions, will be measured using the brief nine item form of the Zimbardo Time Perspective Inventory (ZTPI-R) [52] which includes measures of both present and future orientation. We will also collect data on ethnicity and educational level in order to describe the cohort in comparison to the UK population.

Participants’ views of the risk and/or lifestyle information will also be assessed immediately post intervention by asking participants how much they agreed that the interventions were understandable, trustworthy, useful, motivating, important and well-presented and helped them decide about cancer risk reduction [53]. We will also collect process measures to assess how participants used the intervention using website analytics. These will include the total time spent on the intervention, the time spent viewing the risk information, the number of times participants set target values and view the effect of those changes on the estimates of risk, which lifestyle pages are viewed, and whether participants enter any specific behavioural goals.

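### Intention to change is compared post-intervention only; using the baseline behaviours already collected as covariates would recover some precision for the behaviour-specific items

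*Protocol article*

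**What the plan says.** The secondary objectives name five outcomes: "perceived risk of cancer; anxiety; cancer-related worry; intention to change behaviour; and awareness of cancer risk factors". Table 1 (Measures) gives four of them a baseline assessment. Intention is the exception, with a single assessment immediately after the intervention. The Measures text agrees: "Overall intention to change behaviour will be measured immediately post intervention using four questions on 7-point Likert response scales". The same section adds one 5-point item for each of seven lifestyle behaviours, with a further not-applicable option.

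For continuous secondary outcomes the Statistical analyses section says "Similar analyses will be used to estimate intervention effects on continuous secondary outcome variables", which refers back to the primary model, "with the baseline value included as a covariate in the model (i.e. analysis of covariance, ANCOVA". It then makes an exception: "Intention to change behaviour, self-efficacy and response efficacy are only measured immediately after the intervention so linear regression will be used". Self-efficacy and response efficacy are thus treated in the same way as intention.

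The Baseline assessment and Measures sections state that the questions feeding the risk calculation are asked before randomisation and cannot be left blank. They cover height, weight, smoking, alcohol, physical activity, fruit, vegetables, red meat and processed meat.

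**The concern.** Differences between people in how much they intend to change, present before any risk information is shown, add variance to a post-only comparison. A pre-randomisation measure related to the outcome removes part of it. For perceived risk, anxiety, worry and awareness the plan does this through a baseline. For intention it does not, and it gives the lack of a baseline as the reason for plain linear regression.

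That reason covers only a covariate on the same scale. For the behaviour-specific items a different pre-randomisation variable is available: how much of the behaviour the participant already does. Someone who already exercises a great deal may well answer the item on becoming more active differently from someone who does none.

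At stake is the width of the 98.75% intervals for one secondary outcome. Validity is not in question.

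**Working it through.** **1. Reproducing the protocol's own figure.** It concerns the primary outcome; no power or precision is stated for intention. Inputs from Sample size: difference 0.3, SD 0.97, significance level 1.25% (taken as two-sided, to match the 98.75% intervals), 250 per group less 10% loss = 225, correlation ρ of 0.1, 0.2 or 0.3.

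Power = Φ(0.3 / [0.97·√(1−ρ²)·√(2/225)] − 2.498)

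This gives 78.8%, 80.2% and 82.7%, against the stated 79%, 80% and 83%. The protocol's own calculation therefore uses the variance factor 1−ρ² for baseline adjustment. The same factor is applied below.

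**2. Post-only precision for intention.** Take the outcome in SD units, 250 per group, no loss at the immediate assessment (assumption), 80% power and 1.25% two-sided.

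- Two groups, 250 v 250: (2.498 + 0.842)·√(2/250) = 0.299 SD.
- Control v the three risk groups combined, 250 v 750: (2.498 + 0.842)·√(1/250 + 1/750) = 0.244 SD.

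**3. Behaviour-specific items with the baseline behaviour as covariate.** Let R² be the share of an item's variance explained by the baseline level of that behaviour. The documents give no value, so R² is an assumption. The interval width is multiplied by √(1−R²), and the equivalent gain in sample size is 1/(1−R²) − 1.

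| R² (assumed) | Interval narrower by | Equivalent gain in participants |
|---|---|---|
| 1% | 1 − √0.99 = 0.5% | 1/0.99 − 1 = 1% |
| 10% | 1 − √0.90 = 5.1% | 1/0.90 − 1 = 11% |
| 20% | 1 − √0.80 = 10.6% | 1/0.80 − 1 = 25% |

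These are relative gains among participants who give a scored answer. The not-applicable option will leave fewer than 250 per group for some items, so 0.299 SD is a best case for them. For smoking, most people to whom the item applies are current smokers, so baseline status has little variance left to explain anything.

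**4. Overall intention, if the four items were also asked at baseline.** Here ρ is the correlation between baseline and post-intervention scores. Every row is an assumption for this outcome: the values 0.1 to 0.3 are borrowed from the primary outcome over three months, and 0.5 to 0.7 have no source in the documents.

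| ρ | Interval narrower by | Detectable, 250 v 250 | Detectable, 250 v 750 |
|---|---|---|---|
| 0 (as planned) | – | 0.299 SD | 0.244 SD |
| 0.1 | 0.5% | 0.297 SD | 0.243 SD |
| 0.2 | 2.0% | 0.293 SD | 0.239 SD |
| 0.3 | 4.6% | 0.285 SD | 0.233 SD |
| 0.5 | 13.4% | 0.259 SD | 0.211 SD |
| 0.6 | 20.0% | 0.239 SD | 0.195 SD |
| 0.7 | 28.6% | 0.213 SD | 0.174 SD |

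The table assumes that the extra baseline questions leave the difference between groups unchanged.

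**The case against.** **The plan is consistent and open on this point.** The objectives, Table 1, the Measures text and the analysis section agree, and the reason for the different model is given. A randomised post-only comparison is valid. This stands: the point is about efficiency only.

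**Covariates may be listed in a document not shown.** The sentence does not say the model is unadjusted, and secondary covariates are often left to the SAP. This stands in part. The protocol does tie the model to the lack of an own baseline and mentions no substitute. If the SAP already lists the baseline behaviours as covariates, nothing needs changing.

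**Intention is not singled out.** A reader might infer that it alone among the psychological measures lacks a baseline. Table 1 and the quoted sentence show otherwise, since self-efficacy and response efficacy share its schedule. Nor is it specially protected from three-month drop-out: risk perception, risk conviction, awareness, anxiety and maladaptive coping are also assessed immediately after the intervention.

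**Omitting intention at baseline is defensible.** The four overall items are general statements that could be answered beforehand, and the protocol repeats comparable scales. But consent to the end of the second questionnaire takes at most 45 minutes, and repeating statements of commitment within that time invites consistent answers. That could shrink the difference between groups while raising the very correlation that is credited as gain. It could also prompt controls to change. That this would happen equally in all arms does not make it harmless. This stands, and is why the baseline items are not put forward as a correction.

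**The baseline behaviour may predict intention poorly or non-linearly.** People already meeting a recommendation may disagree or choose not applicable. This limits the gain but does no harm: a pre-randomisation covariate that explains little costs about one degree of freedom and does not compromise the comparison.

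**Conclusion.** The point holds as a minor improvement in efficiency. Intention is a named secondary outcome measured only after the intervention, and its model is set by the absence of its own baseline, while the other four outcomes named in the objectives have one. For the behaviour-specific items the plan leaves unused covariates that are complete and collected before randomisation. Using them is worth about 1% to 25% more participants if they explain 1% to 20% of the variance, with little expected for smoking. That range is an assumption.

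A reader might go further and infer that the intention results would be biased, or that a baseline intention scale is needed and would bring a large gain. The documents support neither. Randomisation protects the comparison. The gain from a baseline scale runs from a 0.5% to 4.6% narrower interval at correlations of 0.1 to 0.3 up to 13% to 29% at 0.5 to 0.7. No correlation for this outcome is given, and anchoring could offset the gain.

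**What to change.** Add one sentence to Statistical analyses after the statement on intention, to the effect that each behaviour-specific intention item will be analysed by linear regression with the participant's baseline level of that behaviour as a covariate. The variables are weight or BMI, alcohol, physical activity, fruit, vegetables, red meat and processed meat. Smoking status may be included for uniformity, though little gain is expected. If the SAP already provides for this, a cross-reference is enough.

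The cost is that sentence: no new questions, no change to the sample size, and about one degree of freedom per model for a continuous covariate.

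Optionally, the sponsor may consider asking the four overall-intention items at baseline and analysing that scale by ANCOVA. This costs four short questions and carries the anchoring risk described above. Keeping the post-only measurement is an acceptable decision, and a short statement of the reason would be enough.
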